### 1.2. Identification of the clinical investigation plan

#### a) Title of the clinical investigation

Human-Prosthetic Interaction: Brain & Technology After Lower-Limb Loss

#### b) Reference number identifying the specific clinical investigation

ClinicTrials.gov Registry Number: Requested

#### c) Version or date of the CIP

Protocol version and date: Version 1 - 13 January 2023

#### d) Summary of the revision history in the case of amendments

| Version | Date        | Comments        |
|---------|-------------|-----------------|
| 1       | 13-JAN-2023 | Initial version |

#### e) Version / issue number and reference number

Version 1 - 13 January 2023.

#### f) Abbreviations and acronyms

|            |                                     |
|------------|-------------------------------------|
| ADL | Activities of Daily Living          |
| CIP | Clinical Investigation Plan         |
| CIR | Clinical Investigation Report       |
| DMC | Data Monitoring Committee           |
| H   | Hypotheses                          |
| IB  | Investigator's Brochure             |
| IFU | Instruction For Use                 |
| MDR | Medical Device Regulation           |
| MRI | Magnetic Resonance Imaging          |
| PEQ | Prosthetic Evaluation Questionnaire |

**QUEST** Quebec User Evaluation of Satisfaction with assistive Technology

**ROs** Research Objectives

**VUB** Vrije Universiteit Brussel

## 1.5. Overall synopsis of the clinical investigation

|                    |                                                                                                                                                                                          |
|--------------------|------------------------------------------------------------------------------------------------------------------------------------------------------------------------------------------|
| Official title     | Human-Prosthetic Interaction: Brain & Technology After Lower-Limb Loss                                                                                                                   |
| Objectives         | The main objective of this investigation is to compare rehabilitation with the LUNARIS® and with usual rigid passive feet.                                                               |
| Endpoints          | Evaluating functional performance and structural brain adaptations when doing rehabilitation with an articulated ankle-foot prosthesis in comparison with a non-articulation prosthesis. |
| Study population   | Healthy people with lower-limb amputation                                                                                                                                                |
| Number of subjects | 40 lower-limb amputees                                                                                                                                                                   |

|                                    |                                                                                                                                                                                                                                                    |
|------------------------------------|----------------------------------------------------------------------------------------------------------------------------------------------------------------------------------------------------------------------------------------------------|
|                                    | 20 able-bodied persons                                                                                                                                                                                                                             |
| Inclusion criteria                 | 
 
• Age: 25 - 65 years
 
• Gender: men and women
 
• Level of amputation: unilateral transtibial
 
• Medicare Functional Classification Level: K3-K4
 
                          |
| Exclusion criteria                 | 
 
• Having metal implants
 
• Bilateral or additional upper-limb amputation
 
• Diabetic of amputation
 
• Neurological disorders
 
• Excessive stump pains and wounds
 
 |
| Date of first enrollment           | September 2023                                                                                                                                                                                                                                     |
| Duration of clinical investigation | At least 2 years                                                                                                                                                                                                                                   |
| Follow-up                          | No follow-up is included in this study                                                                                                                                                                                                             |

*Table 1: Overall synopsis of the clinical investigation*

## 2. Identification and description of the investigational device

### a) Summary description of the investigational device

The LUNARIS® is an external ankle-foot prosthetic component with an articulated ankle-joint and internal sensors. It is intended for the replacement of the ankle-foot to compensate for a lower-limb deficiency. It is to be used exclusively for the non-invasive, exo-prosthetic fitting of the lower limb prosthesis, as prescribed by a healthcare professional. It is designed for single-patient use and supports low to moderate impact use. It is developed to fulfil basic daily activities such as standing, walking, stair ascending and descending, slope ascending and descending, sitting, in indoor and outdoor environments.

The LUNARIS® is delivered with its smart charger, the IO® CHARGER. This smart charger is an accessory intended to charge the LUNARIS® and to transfer the data gathered during the day to the Axiles Bionics secured cloud based service for the purpose of predictive maintenance.

### c) Name or number of the model/type

LUNARIS®

### d) Description as to how traceability shall be achieved during and after the clinical investigation

The study is going to be registered on ClinicalTrials.gov (reference number: requested) and will be open access. The CIP is outlined and the results will be communicated after termination of the study.

### e) Intended purpose of the investigational device in the proposed clinical investigation

The LUNARIS® is an external ankle-foot prosthetic component with an articulated ankle-joint and internal sensors. It is intended for the replacement of the ankle-foot to compensate for a lower-limb deficiency. It is to be used exclusively for the non-invasive, exo-prosthetic fitting of the lower limb prosthesis, as prescribed by a healthcare professional. It is designed for single-patient use and supports low to moderate impact use. It is developed to fulfil basic daily activities such as standing, walking, stair ascending and descending, slope ascending and descending, sitting, in indoor and outdoor environments.

### f) The populations and indications for which the investigational device is intended.

The LUNARIS® is indicated for use as a component in a lower limb prosthesis for individuals with a missing lower-limb, for example due to trauma, vascular disease, cancer or congenital deficiency, including:

- Unilateral or bilateral amputation or deficiency
- Unilateral or bilateral knee disarticulation
- Unilateral or bilateral transfemoral amputation or deficiency
- Unilateral hip disarticulation

## g) Description of the investigational device

The LUNARIS® is a mechanical device which is a component of an external lower limb prosthesis and which is designed to functionally replace, in part or total, a missing ankle-foot complex.

A lower limb prosthesis is commonly composed of multiple components, all assembled and fitted to the amputee by a certified prosthetist. Fig. 1 depicts the different components of a lower-limb prosthesis, consisting of:

- A custom made gel liner (A) - made by the prosthetist - that is wrapped around the residual limb of the amputee (B). The liner is made out of electrically non-conductive materials. The role of the liner is identical to the role of socks in a shoe.
- A custom made hard socket (C) - made by the prosthetist - that is used to fit the residual limb of the amputee (B). The socket is made of solid electrically non-conductive materials, typically manufactured out of fibreglass, carbon fibre infused with acrylic resin, or thermoplastics. Its role is to serve as an interface or attachment to the body of the amputee. Therefore the socket also includes a suspension system to prevent the artificial limb from falling off when the leg is lifted up or moved during gait.
- The shank of the lower limb prosthesis is made by a pylon tube (D), typically manufactured out of steel, aluminium or carbon fibres. This pylon tube is fitted with universal (pyramid or tube) adaptors (E) on both sides to interface the socket on one side, and the ankle-foot component on the other side. Both the pylon tube and adaptors are provided and configured by the prosthetist.
- Lastly, an ankle-foot prosthetic component (F, also referred to as *prosthetic foot*), provided by a legal manufacturer, is attached by the prosthetist to the pylon tube (D) by the means of the universal adaptor (E). The ankle-foot component is typically covered by a foot cover (G). The principle of operation for dorsiflexion/plantar flexion control can be based on various technologies (i.e., electronically driven, mechanical friction/elastic deflection with no fluid or gas operating media, mechanical friction/elastic deflection with fluid or gas operating media).

[figure not shown]

Figure 1: Illustration of a lower limb prosthetic leg with (B) Residual Limb, (A) Gel Liner, (C) Socket, (E) Adaptors, (D) Pylon, (G) Foot Cover and (F) Ankle-Foot Component.

A **Prosthetist** and Orthotist, as defined by The World Health Organisation, is a healthcare professional with overall responsibility of Prosthetics & Orthotics treatment, who can supervise and mentor the practice of other personnel. They are qualified and certified clinicians trained to assess the needs of the user, prescribe treatment, determine the precise technical specifications of prosthesis and Orthosis, take measurements and image of body segments, prepare models of the evaluation, fit devices and evaluate treatment outcome.

It is important to note that **Axiles Bionics only acts as a legal manufacturer of an ankle-foot prosthetic component** (Fig. 1 E-F-G). All other components as described and depicted in Fig. 1 (A-D) are provided and/or made by the prosthetist. The assembly, alignment and tuning to the amputee of the complete lower limb prosthesis is done by the certified prosthetist.

The LUNARIS® is made to fit a normal shoe and connects to the shank (pylon(D) in Fig. 1) through a standard adaptor, which will be used with sockets provided by the healthy subjects. As a result and as explained above, there is no direct contact between the residual limb and the LUNARIS®.

The LUNARIS® is delivered with its smart charger, the IO CHARGER®. This smart charger is an accessory intended to charge the LUNARIS® and to transfer the data gathered during the day to the Axiles Bionics secured cloud based service for the purpose of predictive maintenance.

h) Summary of the necessary training and experience needed to use the investigational device based on risk assessment

The LUNARIS® needs to be fitted and aligned to the lower limb of the subject. Afterwards, basic exercises such as standing, maintaining balance and walking need to be practised so that the subject is able to perform the experimental tasks.

i) Description of the specific medical or surgical procedures involved in the use of the investigational device

Not applicable.

j) References to the IB and IFU

|                               |                                             |
|-------------------------------|---------------------------------------------|
| IB                     | IB_HumanIT                                  |
| IFU of the LUNARIS®    | MDE002_QA-IFU-D001_FINAL_FR-NL-DE-EN_v1.pdf |
| IFU of the IO CHARGER® | MDE003_QA-IFU-D002_FINAL_FR-NL-DE-EN_v1.pdf |

The Investigator Brochure (IB) and the two Instruction For Use (IFU) are attached to this document.

### 3. Justification for the design of the clinical investigation

A first clinical study, led by the VUB, has been conducted with the LUNARIS® Demonstrator. The complete protocol (B.U.N. 143201526629) has been approved by the medical Ethics Committee of the University Hospital of the VUB.

In this study, forty-two participants completed the protocol assessing performance and functional mobility with their current prosthesis and the LUNARIS® Demonstrator. Subjective measures indicated the added value of this device, while overall task performance and intensity of effort did not differ between the LUNARIS® Demonstrator and the current prosthesis. The familiarisation time only lasted between one and two hours, which was not enough to obtain significant results between the LUNARIS® Demonstrator and the current prosthesis of the user [1].

In addition, a systematic review about therapeutic benefits of lower limb prosthesis was performed in 2021. It could be concluded that no studies investigating the long-term therapeutic benefits of performing daily activities with passive, quasi-passive and active ankle-foot prostheses in people with unilateral lower-limb amputation were found, highlighting a gap in the literature [2].

Lastly, further investigations (B.U.N. 143201526629 - Amendment) unravelling both acute and more prolonged adaptations were conducted to evaluate the LUNARIS® Demonstrator. This study revealed a potential long-term benefit of recovering a gait pattern of able-bodied persons after a few months of familiarisation. We hypothesised that it might be a consequence of the high flexibility of the LUNARIS® Demonstrator [3].

As a result, this study aims to demonstrate that doing the rehabilitation with the LUNARIS® may allow the user to recover a gait pattern closer to the one of able-bodied person and that brain plasticity will be less impacted when walking with the LUNARIS® than with another rigid prosthetic device. Studying the effect of the LUNARIS® during rehabilitation could be a great opportunity to investigate the rehabilitation with an articulated ankle prosthesis and the long term benefits of the LUNARIS®.

### 4. Benefits and risks of the investigational device, clinical procedure, and clinical investigation

#### a) Anticipated clinical benefits

The LUNARIS® aims to restore basic functional mobility during daily activities in healthy people with a lower-limb amputation and improve their quality of life. This study aims to demonstrate that doing the rehabilitation with the LUNARIS® may allow the user to recover a gait pattern closer to the one of able-bodied person and that brain plasticity will be less impacted when walking with the LUNARIS® than with another rigid prosthetic device. To the best of the authors' knowledge, currently no studies investigated the long-term therapeutic benefits of prosthetic feet [2]. Studying the effect of the LUNARIS® during rehabilitation could be a great opportunity to fill this gap.

#### b) Anticipated adverse device effects

There are no disadvantages or risks associated with this research. Moreover, previous experiments with the Talaris Demonstrator (the LUNARIS® prototype, registered on B.U.N. 143201526629) have shown that there is a high willingness and motivation from the participants to participate in the experiments. In addition, no side or adverse effects were reported.

#### c) Risks associated with participation in the clinical investigation

The LUNARIS® is a CE-marked medical device. Therefore, risk analysis has been performed according to ISO 14971 to ensure that risks associated with the device are identified, evaluated and controlled.

The risk analysis shows that any residual risks which may be associated with the device are acceptable, when weighed against the benefits of the intended use to the lower-limb amputee, and compatible with a high level of protection of health and safety.

#### d) Possible interaction with concomitant medical treatments as considered under the risk analysis

Not applicable.

#### e) Steps that will be taken to control or mitigate the risks

We ensure that any event as referred to in Article 80(2) of the Medical Device Regulation will be fully recorded by the investigators, manufacturer or other parties, and immediately notified by the sponsor to all competent authorities (including FAMHP) by using the European form in a timely manner.

#### f) Rationale for benefit-risk ratio

The overall residual risk associated with the device is acceptable in relation to the benefits of the intended use of the device. The users may expect more benefits than risks in using the device, therefore, the device does not pose a concern to human health for the intended use.

The Risk Management File is attached to this document.

## 5. Objectives and hypotheses of the clinical investigation

### a) The purpose of the clinical investigation

This clinical investigation aims to study the rehabilitation with the LUNARIS® in comparison to the rehabilitation with usual rigid passive feet.

### b) Objectives

The different research objectives (ROs) are:

**RO.1.1** The primary aim is to investigate the effect of walking performance with a new passive ankle device (LUNARIS®) compared to the current prosthetic ankle device in people with a unilateral lower limb amputation.

**RO.1.2** A second aim is to examine the effect of the different prostheses on postural stability in people with a unilateral lower limb amputation.

**RO.1.3** A third aim is to determine if the type of prosthesis changes the movement pattern during walking in an individual with a unilateral lower limb amputation.

**RO.2** The secondary aim is to examine changes in whole-brain networks related to the type of prosthesis in people with a unilateral lower limb amputation by means of MRI and diffusion tensor imaging.

### c) Scientific justification and clinical relevance for effect sizes

The primary endpoint of the clinical trial is the distance covered during the 6-minutes' walk test. The sample size was calculated based on a study comparing passive and quasi-passive prosthetic ankles which found an effect size Cohens'  $f = 0.318$  on distance covered during the 6-minutes' walk test [4]. A total of 40 participants with a lower limb amputation is required and will be allocated to one of the two prosthetic groups. These individuals will be stratified by age (2 strata:  $< 45$  years,  $\geq 45$  years, block size = 4) to control for age-related cognitive deterioration. A matched control-group of 20 able-bodied individuals will be included to enable comparison. The required number of 40 participants with amputation is based on a sample size calculation for an analysis of variance using G\*Power (version 3.1.9.4) envisaging 10% drop-out. Values used for this calculation were medium expected effect size  $f = 0.318$ , power = 0.80,  $\alpha = 0.05$ , the number of groups = 3 and the number of measurements set at 2 with a correlation between measurements of 0.75.

### d) Primary and secondary hypotheses

The different hypotheses (H) are:

**H1** We hypothesise that people walking with the passive prosthesis (LUNARIS®) will be able to cover significantly more distance (i.e.,  $> 35$ m) during 6-min walking compared to people walking with their current prosthetic device [4][5]. Secondly, we expect that wearing the LUNARIS® will improve postural stability and improve movement patterns after 12 weeks compared to walking with the current ankle prosthesis [6][7][8]. Thirdly, we noticed based on anecdotal evidence that people walking with the LUNARIS® are able to descend stairs more naturally, like able-bodied people. We hypothesise that doing the rehabilitation with the LUNARIS® will help people descending stairs without the need of rolling over the edge of a step, and as a consequence, will reduce the number of falls.

**H2** Based on my literature review on brain neuroplasticity after a lower limb amputation, we hypothesise to discover differences in structural whole-brain networks between participants with the LUNARIS® and current prosthesis after 12 weeks. We assume that these differences in structural networks will be less pronounced among people wearing the LUNARIS® compared to people wearing the current

prostheses [9]. Furthermore, we expect that these disparities in brain structural connectivity will translate into a change in performance on the physical tests.

e) Risks and anticipated adverse device effects that are to be assessed

To date, no device deficiencies have been reported with the LUNARIS®. We are not yet able to give a concise summary of device deficiencies and thus not able to report any deficiency that might have led to a serious adverse event if appropriate action had not been taken, intervention had not occurred, or circumstances had been less fortunate.

The Risk Management File is attached to this document.

## 6. Design of the clinical investigation

### 6.1. General

#### a) Description of the design type of clinical investigation to be performed

This cohort study includes three groups.

- 20 lower-limb amputees who are going to do their rehabilitation and perform daily activities with a new articulated ankle foot prosthesis: the LUNARIS®.
- 20 lower-limb amputees who are going to do their rehabilitation and perform daily activities with a conventional prosthetic ankle: the SACH® followed by the most suited prosthesis for them.
- 20 able-bodied subjects which will be used as a control group.

#### b) Description of the measure to be taken to minimise or to avoid bias

All appointments for the MRI will take place at UZ Brussel to avoid any bias due to a different MRI scanner. All appointments for functional performance testing will take place at Axiles Bionics to avoid any bias due to different slopes or staircases between subjects and between sessions.

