## e) Equipment to be used for assessing the clinical investigation variables

### Functional performance testing

Functional balance will be examined. Table 2 lists the different tests. A 6-min walking test, dual-task L-test, L-test, slope walking test, and stairs climbing and descending test will indicate functional balance and dual-task performance. Rating of perceived exertion [16], level of fatigue and comfort [17] and NASA-Task Load index (NASA-TLX) assessing perceived workload [18] will be assessed after each task.

| Performance tests                       | Outcome                       | Materials                   |
|-----------------------------------------|-------------------------------|-----------------------------|
| Slope walking test [19]                 | Time to complete test         | Stopwatch                   |
|                                         | Biomechanical gait parameters | Inertial measurements units |
| Stair climbing and descending test [20] | Time to complete test         | Stopwatch                   |
|                                         | Biomechanical gait parameters | Inertial measurements units |
| Dual-task L-test [21]                   | Time to complete test         | Stopwatch                   |
|                                         | Accuracy of subtractions      | Audio-recorder              |
| L-test [21]                             | Time to complete test         | Stopwatch                   |
| 6-min walking test [5]                  | Distance covered in 6 minutes | Measuring wheel             |
|                                         | Biomechanical gait parameters | Inertial measurements units |

Table 2: Physical performance tests

The primary endpoint is the distance covered during the 6-min walking test. Any difference found between the different prostheses on the distance travelled will be considered clinically relevant from a difference of 35 metres [5]. Secondary endpoints will comprise performance on the L-test, dual-L-test, slope walking test and stairs climbing and descending test, and the evaluation of the gait pattern.

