## 6.4. Procedures

### a) Description of all clinical investigation-related procedures that subjects undergo during the clinical investigation

*Lower-limb amputees:*

There are three measurement moments for lower-limb amputees which will be divided into four days.

**Day 1:** the subject will be expected at the radiology department at UZ Brussel. Here, a non-invasive brain scan will be taken under the supervision of [name]. [name] (department head of Radiology). This measurement moment will take approximately 60 minutes.

**After 12 weeks:** the subject will be expected at Axiles Bionics for a series of non-invasive tests. This measurement moment will take approximately 120 minutes.

**After 24 weeks:** this measurement moment will be divided into two days. The subject will be expected on day 1 at the radiology department at UZ Brussel. Here, the same brain scan will be taken as described in measurement moment 1. This measurement moment will take about 60 minutes. On day 2, the subject will be expected at Axiles Bionics for a series of non-invasive tests as described in measurement moment 2. This measurement moment will take about 120 minutes.

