### b) Description of those activities performed by sponsor representative

The sponsor is responsible for the execution of the experimental tasks, data gathering and analyses.

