### e) Sample size calculation and justification

The primary endpoint of the clinical trial is the distance covered during the 6-minutes' walk test. The sample size was calculated based on a study comparing passive and quasi-passive prosthetic ankles which found an effect size Cohens'  $f = 0.318$  on distance covered during the 6-minutes' walk test [4]. A total of 40 participants with a lower limb amputation is required and will be allocated to one of the two prosthetic groups. These individuals will be stratified by age (2 strata:  $< 45$  years,  $\geq 45$  years, block size = 4) to control for age-related cognitive deterioration. A matched control-group of 20 able-bodied individuals will be included to enable comparison. The required number of 40 participants with amputation is based on a sample size calculation for an analysis of variance using G\*Power (version 3.1.9.4) envisaging 10% drop-out. Values used for this calculation were medium expected effect size  $f = 0.318$ , power = 0.80,  $\alpha = 0.05$ , the number of groups = 3 and the number of measurements set at 2 with a correlation between measurements of 0.75.

- f) The rationale for the number of procedures to be performed by a single user as part of the learning curves

A baseline experiment with a conventional prosthetic ankle used in rehabilitation is required to observe any similarities or differences in outcomes with the LUNARIS®. Moreover, a baseline experiment with able-bodied subjects is required to observe any similarities or differences in outcomes with the LUNARIS®. Therefore, each lower-limb amputee is asked to schedule four appointments and each able-bodied subject is asked to schedule two appointments to run through the whole experiment.

- g) Pass / Fail criteria to be applied to the results of the clinical investigation

Not applicable.

- h) The provision for an interim analysis

Not applicable.

- i) Management of bias

All appointments for the MRI will take place at UZ Brussel to avoid any bias due to a different MRI scanner. All appointments for functional performance testing will take place at Axiles Bionics to avoid any bias due to different slopes or staircases between subjects and between sessions.

- j) Management of potential confounding factors

Not applicable.

- k) Description of procedures for multiplicity control and adjustment of error probabilities

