#### b) Procedures used for CRF tracking

The pre-processing (basic filters and artefact removal) steps will be performed by the co-investigators to ensure data quality.

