#### d) Procedures to maintain and protect subject privacy

As personal information is branded by the EU as sensitive, data will be anonymized as soon as possible. Participants will receive a code corresponding to their inclusion order, and the file that relates these codes to their personal information will be encrypted. During the course of the study, data will only be stored with personal access, on a personal cloud server. After the study completion, all data will be shared with the research lab through a network attached storage.

As personal and sensitive data of human participants will be collected, pseudonymisation of the data will take place as soon as possible upon data acquisition. The file which establishes the link between the pseudonymised identities and the identification of the participant, will be password-protected.

The data protection officer of the VUB ([contact]) will be notified of our study. Data in the present study will be managed confidentially, conforming to the Algemene Verordening Gegevensbescherming (GDPR) of 27 April 2016.

Participating in this study means that the participant agrees that the investigators gather data of the participant that will be used to conduct the investigation and eventually will result in the publications in scientific journals and presentations at conferences. The participant will always have the right to ask the investigators which data he/she has gathered on them and for what this data is used in light of the investigation. The participant retains the right to look into this data and to ask for corrections on the occasion this data would contain errors. The participant also retains the right to stop his/her participation in the study at any moment.

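### The bias sections standardise only the scanner and the test venue; nothing guards against performance or detection bias in a non-randomised study whose functional tests are run at the device manufacturer's premises

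*Protocol*

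**What the plan says.** Two headings in the protocol are reserved for bias, 6.1 b and 7 i. Both give the same two measures. For imaging: "All appointments for the MRI will take place at UZ Brussel to avoid any bias due to a different MRI scanner". For function: "All appointments for functional performance testing will take place at Axiles Bionics to avoid any bias due to different slopes or staircases".

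The visit schedule in section 6.4 a confirms the venue. At week 12 "the subject will be expected at Axiles Bionics for a series of non-invasive tests", and the week 24 functional tests and the able-bodied group's tests are held there too. Section 2 g identifies the owner of the venue: "Axiles Bionics only acts as a legal manufacturer of an ankle-foot prosthetic component".

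On outcomes, section 6.1 e says: "The primary endpoint is the distance covered during the 6-min walking test". Distance is read with a measuring wheel. The slope, stair and L-tests are timed by stopwatch, and subtraction accuracy is taken from an audio recording. Exertion, fatigue, comfort and workload are rated after each task.

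On data handling, section 8 b says: "The pre-processing (basic filters and artefact removal) steps will be performed by the co-investigators to ensure data quality". Section 14 j has the co-investigators analyse the data under the principal investigator's control. Section 6.1 e says that the biomechanical data are cleaned in Matlab. Section 6.3 e states that there is no randomisation.

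**The concern.** A participant cannot be blinded to a prosthetic foot, so the comparison between prostheses is open in practice. Bias can then enter by two routes.

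- **Performance bias.** How far someone walks in six minutes depends on effort and on what the tester says. Here the participant knows the foot and is tested on the premises of the company that makes one of the feet being compared. Hypothesis H1 (section 5 d) predicts the direction of the result.
- **Detection bias.** Someone who knows the arm may time, score or reject data differently without intending to. The people who decide what counts as an artefact also analyse the results.

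The first route bears on the primary endpoint, the timed tests and the ratings made on site. The second bears on stopwatch timing, audio scoring, gait parameters and brain connectivity. One venue and one scanner remove differences between places, but they act on neither route. If LUNARIS did better, the plan would offer no design feature with which to answer the charge of expectation or observer effects.

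**Working it through.** The protocol gives no figure on this point, so the check is a comparison of its sections.

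1. **Measures listed under bias.** 6.1 b: one MRI site, one functional-test site. 7 i: the same two. Neither mentions masking, tester conduct or scoring.
2. **Masking elsewhere.** No section masks participants, testers, data processors or analysts. Section 16 b carries a heading about breaking a masking code, but its text covers early termination and voluntary participation and names neither a code nor a masked role.
3. **Other safeguards.** Age stratification (5 c, 7 e) and covariate adjustment (7 b) deal with differences between the groups' members, not with how outcomes are produced or recorded. Independent analysis by the investigators (7 k) is not said to be masked and is placed under multiplicity.
4. **Timing.** Under section 6.1 d both functional assessments, at weeks 12 and 24, come after allocation, so neither is free of knowledge of the foot. The first MRI is acquired before allocation, but the protocol does not say when it is processed.
5. **Which outcomes each route reaches.**
   - Setting, effort and tester conduct: walk distance, stopwatch times, ratings after each task.
   - Cleaning: gait parameters (6.1 e refers to cleaning of biomechanical data) and, by inference, MRI. Section 8 b names no data type.
   - Cleaning does not reach the wheel-measured distance.

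**Illustration only, with an assumed bias.** Take no true effect, a systematic shift of *b* standard deviations towards one arm, and a two-sided two-sample t-test at 5% (the protocol gives 5% but not the sidedness). The test statistic is noncentral t with 2*n* − 2 degrees of freedom and noncentrality *b*·√(*n*/2).

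- *n* = 20 per arm (section 6.1 a), √(20/2) = 3.162:
  - *b* = 0.10: noncentrality 0.316, rejection rate 6.1%
  - *b* = 0.25: noncentrality 0.791, rejection rate 12.0%
  - *b* = 0.50: noncentrality 1.581, rejection rate 33.8%
- *n* = 18 per arm (20 × 0.9, the planned 10% drop-out), √(18/2) = 3:
  - *b* = 0.10: noncentrality 0.30, rejection rate 6.0%
  - *b* = 0.25: noncentrality 0.75, rejection rate 11.3%
  - *b* = 0.50: noncentrality 1.50, rejection rate 30.8%

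The values of *b* are not taken from the protocol. It gives no standard deviation for walk distance, so they cannot be turned into metres or set against the 35 m relevance threshold.

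**The case against.** A single venue is a sensible choice: it does remove differences in slopes and staircases. Detailed processing rules are often kept in a statistical analysis plan or an imaging manual, and neither is at hand. That part stands, so the absence of cleaning rules is not in itself a finding. Whether any role is masked is different. It is a design decision that belongs in the protocol, and both bias sections are filled in without it.

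A reader might also infer several stronger points that the document does not support.

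- **That manufacturer staff run the tests.** Section 6.4 b says: "The sponsor is responsible for the execution of the experimental tasks, data gathering and analyses". Sections 4 e and 14 e mention sponsor and manufacturer separately, and the pages on sponsor, investigators, external organisations and site are not in the text available. University investigators may already do all the testing.
- **That the participant code reveals the arm.** Section 8 d says: "Participants will receive a code corresponding to their inclusion order". An order number does not itself carry the arm, and the linking file is encrypted.
- **That MRI and gait files are known to be cleaned unmasked and at discretion.** This is inferred from silence. Basic filtering in Matlab could equally be a fixed pipeline.
- **That every bias favours LUNARIS.** For artefact rejection in MRI or sensor data the direction is unknown.
- **That extra encouragement would be worth about 35 m.** The protocol has no figure for such an effect.
- **That satisfaction is rated at the manufacturer's site.** Section 6.1 d gives no venue for that questionnaire.

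**Conclusion.** The concern holds within these limits. Sections 6.1 b and 7 i control location and nothing else, while the study is non-randomised, its effort-dependent primary test is run at the premises of the LUNARIS manufacturer, and the same people clean and analyse data. Bias from setting, effort and tester conduct could favour LUNARIS on the walk, timed and self-rated outcomes. Unmasked cleaning could distort gait and MRI outcomes either way and leaves the primary distance untouched.

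The size is unknown. The rejection rates above show only how quickly a nominal 5% test degrades under an assumed shift. The conclusion rests on two readings: that silence on masking means none is planned, and that the cleaning in section 8 b includes MRI. The gap does not invalidate the study, but it should be closed because doing so costs little.

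**What to change.** Add to sections 6.1 b and 7 i:

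1. **Coded files.** Relabel MRI, inertial-sensor and audio files with random codes. Complete pre-processing, artefact rejection and subtraction scoring under rules set beforehand, and only then link the arm key.
2. **One script.** Use a single fixed wording for instructions and encouragement in the 6-minute walk and the timed tests, the same for all three groups and at every session.
3. **Testers.** If existing investigators already run the tests, state that manufacturer personnel neither administer nor record them.

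The venue, tests and sample size stay as they are. The cost is a relabelling step, a one-off script and a short delay before files can be processed. Masking will be incomplete: sensor signals may still partly reveal the foot type, and participants will know which foot they wear. The report should state this residual limitation.
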